## Data Safety Monitoring

### Adverse Event Documentation

To protect the safety of the individual treated patients and others who may receive the drug in future, complete records of adverse events will be provided.

### Adverse Event Definition

An adverse event (AE) is any untoward medical occurrence in a patient administered a pharmaceutical product and that does not necessarily have a causal relationship with this treatment. An adverse event can therefore be any unfavorable and unintended sign (including an abnormal laboratory finding), symptom, or disease temporally associated with the use of a medicinal product, whether or not related to the medicinal product. Pre-existing conditions that worsen after drug administration will be reported as adverse events. Generally an increase/worsening of pre-existing disease status more than 30% of baseline is reported as an adverse event (for e.g., a baseline heart rate increase from 150/min to more than 195/min, an increase of FiO_2_ requirement from a baseline 50% to more than 65%).

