#### The Development of Clinically Significant Portal Hypertension

The natural history of fibrotic liver disease can be divided into stages that are relevant to survival and therefore to the development of therapeutic interventions. Some patients will have a cause for chronic liver injury that is amenable to therapy, for example, long-term antiviral therapy in chronic hepatitis B can control viral replication and therefore inhibit immune mediated liver injury, resulting in cirrhosis reversal. For patients with persistent liver injury for which no treatment is available or in whom treatment fails, fibrosis will progress. The onset of clinically significant portal venous hypertension is considered the ‘tipping point’ in this progression as patients who develop it are at risk of developing ascites, variceal hemorrhage, and porto-systemic shunting with hepatic encephalopathy – all events which define the progression from compensated to decompensated cirrhosis.

Measurement of the gradient between venous pressure in the hepatic vein and that in the portal vein [hepatic venous pressure gradient (HVPG)] is widely accepted as the most accurate way to define the severity of portal hypertension and thus the risk of developing death. An HVPG ≥ 10 defines clinically significant portal hypertension. Annual mortality rates increase from 1% in patients with compensated cirrhosis (HVPG 6–10 mmHg) to 3% in compensated cirrhosis with an HVPG ≥ 10 but ≤ 12 mmHg to 10–30% in decompensated cirrhosis (HVPG > 12 but ≤ 16 mmHg) or >60% in patients with very high portal pressures (>16 mmHg). Therefore portal pressure reduction is a therapeutic goal since a decrease in HVPG of ≥20% from baseline or to ≤12 mmHg reduces the risk of variceal bleeding and other complications of portal hypertension such as ascites (D’Amico et al., 2006).

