## Outcomes

### Primary (Assessment of Safety)

(a)Local skin reactions – extravasation, erythema, edema.(b)Anaphylaxis – acute deterioration of respiratory, cardiovascular parameters:Respiratory deterioration – dyspnoea, hypoxema, any requirement for supplemental oxygen or mechanical ventilation.Cardiovascular deterioration – hypotension, hypertension, bradycardia, tachycardia, rhythm abnormalities.(c)Infection – clinical signs, laboratory evidence (increase in CRP, white cell counts, bacterial/viral growth on sterile cultures).(d)Features of rejection as evidenced by impairment in hepatic or renal parameters.Hepatic – new onset jaundice, elevation of hepatic enzymes, coagulation dysfunction – thrombocytopenia, increase in INR.Renal – decrease in eGFR.

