### Adverse Event Severity and Relationship to hAEC

The severity of AEs will be graded using the National Cancer Institute Common Terminology Criteria for Adverse Events (NCI-CTCAE), v4.0. For AEs that are not identified in the NCI-CTCAE, the following scale will be used:

Grade 1: Mild

Grade 2: Moderate

Grade 3: Severe

Grade 4: Life-threatening or disabling

Grade 5: Death related to an AE.

**Causality assessment** will be made using the following definitions:

Unrelated:

This category is applicable to adverse events that are judged to be clearly and incontrovertibly due to extraneous causes (disease, environment, etc.) and do not meet the criteria for drug relationship listed under Unlikely, Possible or Probable.

Unlikely:

In general, this category is applicable to an adverse event that meets the following criteria (must have the first two):

(1)It does not follow a reasonable temporal sequence from administration of the drug.(2)It may readily have been produced by the patient’s clinical state, environment or toxic factors, or other modes of therapy administered to the patient.(3)It does not follow a known pattern of response to the suspected drug.(4)It does not reappear or worsen if or when the drug is re-administered.

Possible:

This category applies to adverse events for which the connection with hAEC appears unlikely but cannot be ruled out with certainty. An adverse event may be considered possibly related if or when (must have the first two):

(1)It follows a reasonable temporal sequence from administration of the drug.(2)It may have been produced by the patient’s clinical state, environment or toxic factors, or other modes of therapy administered to the patient.(3)It follows a known pattern of response to the suspected drug.

Probable:

This category applies to adverse events that are considered with a high degree of certainty to be related to hAEC. An adverse event may be considered probable, if (must have the first three):

(1)It follows a reasonable temporal sequence from administration of the drug.(2)It cannot be reasonably explained by the known characteristics of the patient’s clinical state, environment or toxic factors, or other modes of therapy administered to the patient.(3)It disappears or decreases on cessation or reduction in dose.(4)It follows a known pattern of response to the drug.(5)It reappears on re-challenge.

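### The 30%-of-baseline rule for reporting worsening as an adverse event conflicts with the sentence before it and with the primary safety list, and does not suit compensated cirrhosis

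*Protocol article*

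**What the plan says.** All references are to the Protocol article.

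- **Adverse Event Definition, general wording.** An AE can be "any unfavorable and unintended sign (including an abnormal laboratory finding"), with no minimum size.
- **Adverse Event Definition, pre-existing disease.** First, without a threshold: "Pre-existing conditions that worsen after drug administration will be reported as adverse events". Then, with one: "Generally an increase/worsening of pre-existing disease status more than 30% of baseline is reported as an adverse event". Two examples follow: "a baseline heart rate increase from 150/min to more than 195/min", and an FiO2 requirement going from 50% to above 65%.
- **Outcomes, Primary (Assessment of Safety).** Under features of rejection the list gives "elevation of hepatic enzymes, coagulation dysfunction" (with thrombocytopenia and INR increase) and, for the kidney, "decrease in eGFR". No size is attached to any of them.
- **Adverse Event Severity and Relationship to hAEC.** CTCAE enters here as the grading scale: "The severity of AEs will be graded using the National Cancer Institute Common Terminology Criteria for Adverse Events (NCI-CTCAE), v4.0".
- **The Development of Clinically Significant Portal Hypertension.** HVPG of 10 mmHg or more marks clinically significant portal hypertension. Annual mortality is given as 1% at 6–10 mmHg, 3% from 10 to 12 mmHg, and 10–30% above 12 and up to 16 mmHg, the last band being labelled decompensated cirrhosis. On improvement it says that "a decrease in HVPG of ≥20% from baseline or to ≤12 mmHg reduces the risk of variceal bleeding".

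**The concern.** Safety and tolerability are the only primary objective, in 12 open-label patients. What counts as an adverse event is therefore the main measurement of the trial. Two sentences that stand next to each other give different answers for worsening of existing disease, and the word 'generally' leaves each assessor to choose between them. The stricter of the two also disagrees with the primary outcome list.

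Every enrolled patient has pre-existing liver disease, so this is the ordinary case and not an exception. At stake is whether a moderate deterioration of the disease under study enters the AE record, and whether two assessors would record the same change alike.

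**Working it through.** **1. Reproduce the stated threshold.** Heart rate: 195/150 − 1 = 0.30. FiO2: 65/50 − 1 = 0.30. Both examples equal +30% exactly, so the rule is a flat relative change: worsening is reported when the new value exceeds 1.3 × baseline.

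**2. Do the examples fit the population?** Participants are adults aged 18 to 70 recruited from liver clinics. Heart failure, obstructive airways disease and pulmonary hypertension are exclusions. A baseline heart rate of 150/min or a baseline FiO2 of 50% does not describe them. No liver measure is named, so the rule does not say which measure of disease status it applies to.

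**3. Set the rules side by side.** Take a patient whose INR or liver enzyme is abnormal at baseline value *b* because of cirrhosis, and rises to a value above *b* but no higher than 1.3*b*.

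| Text | Is the rise counted? |
|---|---|
| Primary (Assessment of Safety) | Can be: INR increase or enzyme elevation, no size given |
| Adverse Event Definition, sentence without threshold | Yes: any worsening |
| Adverse Event Definition, 30% sentence | Generally no |

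The same change can be a primary safety outcome and fall below the AE line.

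**4. Apply the rule to HVPG.** The baseline range is taken as 6–10 mmHg, the compensated range in the Inclusion Criteria. The cut-points are 10 and 12 mmHg.

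| Baseline (mmHg) | 30% line = 1.3 × baseline | Rise needed to reach 10 | Rise needed to reach 12 |
|---|---|---|---|
| 6 | 7.8 | 66.7% | 100.0% |
| 7.5 | 9.75 | 33.3% | 60.0% |
| 8 | 10.4 | 25.0% | 50.0% |
| 9 | 11.7 | 11.1% | 33.3% |
| 9.5 | 12.35 | 5.3% | 26.3% |
| 10 | 13.0 | already there | 20.0% |

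The lowest baselines at which a cut-point can be met without exceeding +30% are:

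- 10 mmHg: 10/1.3 = 7.69
- 12 mmHg: 12/1.3 = 9.23, so a baseline above 9.23 can pass 12

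For example, 10 to 12.9 mmHg is 12.9/10 − 1 = +29%, which is below the line but above 12. For baselines from 6 to about 7.6 mmHg, reaching 10 takes more than 30%, so the rule does catch that rise.

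**The case against.** **The surrounding wording softens the rule.** The 30% sentence says 'generally', and the broader sentences could still bring a smaller worsening in. HVPG change is a named secondary objective and is measured at follow-up, so a rise would be seen whether or not it is coded as an AE. Clinical decompensation would be an AE in its own right. All of this stands. The rule can leave worsening out of the AE record; it does not make it invisible. But a threshold that works only when assessors set it aside is badly fixed.

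**Cut-offs for the primary list are detail that an article leaves to the full protocol.** This also stands, and their absence is not the point. The point is that a threshold is stated, and it conflicts with text in the same article.

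Several stronger readings are tempting, but the documents do not support them:

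- *CTCAE is a third competing rule.* It grades the severity of events that are already AEs, which is a later step. A clash with its laboratory limits could be shown only from tables that the article does not contain.
- *An eGFR fall from 70 to 49.1 (70 × 0.701, −29.9%) escapes reporting.* Renal insufficiency, defined as eGFR below 70, is an exclusion. Such a fall would be a new abnormal finding, covered by the general AE wording. A similar argument applies to CRP, which is not a pre-existing disease.
- *The AE rate could be anywhere from near 0% to near 100%.* The upper end assumes seven laboratory values, each with a 50% chance of drifting adversely (1 − 0.5^7 = 0.992 if independent). It also assumes that any drift counts as rejection. The list speaks of impairment as evidence of rejection, not of random movement, and nothing in the article establishes the lower end.
- *HVPG shows the clash with the primary list.* HVPG is not on that list. It shows only that a flat 30% suits this disease badly.
- *A rise from 10 to 12.9 mmHg takes a patient from 1% to 10–30% annual mortality.* At exactly 10 mmHg the article's bands overlap (1% and 3%), and the 10–30% figure is attached to decompensated cirrhosis.

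**Conclusion.** The point holds as a conflict over when worsening of existing disease counts. Adverse Event Definition contradicts itself (any worsening against more than 30%), and its 30% figure contradicts the unsized items in the primary safety list. The affected zone is any INR or enzyme worsening of up to 30% from an abnormal baseline. For HVPG it covers baselines from about 7.7 mmHg (reaching 10) and above 9.23 mmHg (passing 12), within an assumed baseline range of 6–10 mmHg. How many of the 12 patients would fall there cannot be derived from the article.

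This should be fixed, but it need not hold up the trial. Escalation turns on serious adverse events, which are defined and reported under separate text, so it is not directly affected. The result rests on reading 'disease status' as including laboratory and haemodynamic measures of liver disease, which the article neither states nor excludes.

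**What to change.** 1. Delete the 30% sentence and its two examples from Adverse Event Definition.
2. Put Adverse Event Definition and the laboratory items in the primary safety list under one reporting threshold for laboratory and vital-sign worsening. One workable choice is a rise of at least one CTCAE v4.0 grade from the patient's own baseline, since that scale is already adopted. Before fixing it, check against the scale that each listed item has usable grades.
3. Leave the existing wording on abnormal laboratory findings in force for new abnormalities, so that the grade-shift rule does not narrow it.
4. List HVPG worsening separately, including every crossing of 10 or 12 mmHg, the cut-points the article already uses. Do not carry over the 20% figure: it describes benefit from a decrease and gives no support as a threshold for harm.

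The cost is protocol wording. The laboratory tests, HVPG and CTCAE grading are already planned, so no new data are needed. The downside is that some more low-grade AEs will be recorded than under the 30% rule; how many cannot be estimated from the article.

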### Adverse Event Severity and Relationship to hAEC

The severity of AEs will be graded using the National Cancer Institute Common Terminology Criteria for Adverse Events (NCI-CTCAE), v4.0. For AEs that are not identified in the NCI-CTCAE, the following scale will be used:

Grade 1: Mild

Grade 2: Moderate

Grade 3: Severe

Grade 4: Life-threatening or disabling

Grade 5: Death related to an AE.

**Causality assessment** will be made using the following definitions:

Unrelated:

This category is applicable to adverse events that are judged to be clearly and incontrovertibly due to extraneous causes (disease, environment, etc.) and do not meet the criteria for drug relationship listed under Unlikely, Possible or Probable.

Unlikely:

In general, this category is applicable to an adverse event that meets the following criteria (must have the first two):

(1)It does not follow a reasonable temporal sequence from administration of the drug.(2)It may readily have been produced by the patient’s clinical state, environment or toxic factors, or other modes of therapy administered to the patient.(3)It does not follow a known pattern of response to the suspected drug.(4)It does not reappear or worsen if or when the drug is re-administered.

Possible:

This category applies to adverse events for which the connection with hAEC appears unlikely but cannot be ruled out with certainty. An adverse event may be considered possibly related if or when (must have the first two):

(1)It follows a reasonable temporal sequence from administration of the drug.(2)It may have been produced by the patient’s clinical state, environment or toxic factors, or other modes of therapy administered to the patient.(3)It follows a known pattern of response to the suspected drug.

Probable:

This category applies to adverse events that are considered with a high degree of certainty to be related to hAEC. An adverse event may be considered probable, if (must have the first three):

(1)It follows a reasonable temporal sequence from administration of the drug.(2)It cannot be reasonably explained by the known characteristics of the patient’s clinical state, environment or toxic factors, or other modes of therapy administered to the patient.(3)It disappears or decreases on cessation or reduction in dose.(4)It follows a known pattern of response to the drug.(5)It reappears on re-challenge.

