## Data Collection and Analyses

Data will be collected prospectively and each individual patient will be monitored and outcomes reviewed following each administration of hAECs. If at any point, significant adverse events are noted directly or indirectly attributable to the hAECs, further recruitment of patients will be stopped pending review by the DSMB and investigators.

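### The causality categories are not mutually exclusive: on the numbered criteria Unrelated cannot be reached, and if the Possible lead-in binds, the low end of the scale runs backwards

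*Protocol article*

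**What the plan says.** All the definitions are in the protocol article, section Adverse Event Severity and Relationship to hAEC.

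- **Unrelated** has two conditions. The event is "judged to be clearly and incontrovertibly due to extraneous causes (disease, environment, etc", and it must fail the other categories: "and do not meet the criteria for drug relationship listed under Unlikely, Possible or Probable".
- **Unlikely** is introduced by "In general, this category is applicable to an adverse event that meets the following criteria (must have the first two". The two required items are "It does not follow a reasonable temporal sequence from administration of the drug" and "It may readily have been produced by the patient’s clinical state, environment or toxic factors, or other modes of therapy administered to the patient".
- **Possible** opens with events for which "the connection with hAEC appears unlikely but cannot be ruled out with certainty". Its two required items are a reasonable temporal sequence and "It may have been produced by the patient’s clinical state, environment or toxic factors, or other modes of therapy administered to the patient".
- **Probable** requires, among other things, that the event cannot reasonably be explained by that same list of other causes.

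Attribution is used elsewhere. Under Data Collection and Analyses: "If at any point, significant adverse events are noted directly or indirectly attributable to the hAECs, further recruitment of patients will be stopped", pending review. Under Serious Adverse Event Reporting, the DSMB evaluates each SAE's relationship to hAEC, and a new event related to hAEC that raises safety concern leads to notification of regulators, the ethics committee and treating physicians.

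**The concern.** A causality scale should give each event one grade, and its lowest grade should be open to events that plainly have another cause. Here the lowest grade is conditional on failing criteria that such events satisfy by their nature.

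This matters more than it would in a controlled trial. The study is open label, has 12 patients and no control group, and its primary objective is safety and tolerability. Attribution is thus the main means of separating an effect of the cells from background illness. Events with other causes are to be expected: the patients have cirrhosis, and the Adverse Event Definition section counts worsening of pre-existing conditions as an adverse event. In so small a study, a few grades that depend on how the assessor reads the definitions can visibly change the causality table.

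**Working it through.** The document gives no figure on this point, so the check is one of logic.

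**Inputs**, all from the causality definitions:

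- X: the event is clearly and incontrovertibly extraneous.
- A: it may have been produced by a cause on the list (clinical state, environment or toxic factors, other therapy).
- T: it follows a reasonable temporal sequence.
- D: it resolves on cessation or dose reduction. This matters only for Probable.

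**Mandatory criteria:**

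- Unlikely = not T, and A.
- Possible = T, and A. If the lead-in is binding, also not X, because a link that can be excluded with certainty is outside the category.
- Probable = T, not A, and D.
- Unrelated = X, and none of the three above.

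**Step 1. The extraneous cause is of a listed type, so X implies A.** A rules out Probable. T is either true or false, and D does not matter, so each row below stands for two patterns (D yes, D no).

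| Timing reasonable? | Numbered criteria only | Possible lead-in also binding |
|---|---|---|
| No | Unlikely | Unlikely |
| Yes | Possible | Unrelated |
| Patterns that reach Unrelated | 0 of 4 | 2 of 4 |

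In the first reading the category is unreachable, because the first criteria of Unlikely and Possible negate each other and an extraneous event satisfies the second criterion of both. In the second reading it can be reached, but only by events whose timing is compatible with a drug effect. The weaker temporal case gets the grade nearer to drug relationship.

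**Step 2. Some extraneous causes lie outside the list.** The wording of Unrelated leaves its examples open-ended, so X might hold without A. There are then 8 patterns (T, A and D each yes or no). Treating an incontrovertibly extraneous event as never Probable, Unrelated is reached in 4 of 8 on the numbered criteria and in 6 of 8 with the lead-in binding. The 2 patterns with a listed cause and no reasonable timing go to Unlikely in both readings.

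**Step 3. Two illustrative records.**

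- A fracture in a road accident on day 3, with the timing judged reasonable: Possible on the numbered criteria, Unrelated if the lead-in binds.
- A fall 14 months after infusion, with the timing judged not reasonable: Unlikely in both readings, although its cause is plainly environmental.

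The first record shows two text-compliant grades for one event. The second shows a plainly extraneous event barred from Unrelated in both readings.

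**The case against.** The strongest reply is that the opening sentence of Possible controls that category. If a cause is incontrovertibly extraneous, the link to hAEC has been ruled out, so the event is not Possible and can be Unrelated. The criteria of Possible are also permissive, and the list for Unlikely is prefaced as a general rule. This stands in part. A reader might infer that Unrelated is empty on every reading, and the documents do not support that; it is empty on the numbered criteria. But the reply leaves the scale inverted, and the required pair is the only operative test given for Unlikely.

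Other stronger inferences also fail:

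- *Every extraneous event in the 5 days after infusion must be graded at least Possible.* The protocol does not define a reasonable temporal sequence or equate it with the 5-day observation period. An event in that period may be judged Unlikely.
- *Events from HVPG catheterisation will be swept in soon after infusion.* Table 2 and the monitoring section place HVPG at screening and at week 8 or later.
- *A number of misgraded events can be calculated.* The document gives no background event rate and no proportion that would be incontrovertibly extraneous.
- *Dose escalation is affected.* Study Design ties escalation to any SAE, whatever its cause. All SAEs go to the DSMB whether or not they are considered related, and the DSMB makes its own assessment. The primary safety outcomes are not filtered by causality grade.

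It is also true that no section ties the recruitment pause to a particular grade or says that Possible counts as related.

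**Conclusion.** The point holds as an internal contradiction in the causality definitions. On the numbered criteria, an extraneous event of a listed type can never be Unrelated (0 of 4 patterns). With the Possible lead-in binding, 2 of 4 can, in inverted order. In both readings, a listed-type extraneous event without reasonable timing is barred from Unrelated.

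This assumes that an event clearly due to disease or environment also counts as one that may readily have been produced by clinical state or environment, and that the mandatory pair of Unlikely is applied as written.

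The reach is limited to the causality tabulation and to judgements resting on attribution: the recruitment pause, the DSMB's relationship review and the related-event notification. The size of any misgrading cannot be estimated. It is still worth correcting, because safety is the primary objective, there is no control group, and the correction is small.

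**What to change.** In Adverse Event Severity and Relationship to hAEC:

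1. Delete from the definition of Unrelated the words "and do not meet the criteria for drug relationship listed under Unlikely, Possible or Probable".
2. State that Unrelated is assessed first and takes precedence, regardless of timing, when the cause is clearly and incontrovertibly extraneous.
3. Reserve Unlikely and Possible for events whose other cause is not certain.

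Under either reading this makes Unrelated reachable and removes the inversion.

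The cost is a short edit to the definitions and to any matching help text on the case report form. The downside is that assessors may use Unrelated somewhat more freely. The demand that the other cause be clear and incontrovertible limits this for all events, and the DSMB's own review limits it further for SAEs.

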## Methods and Analysis

### Study Design

In this open label phase 1 study, the safety and tolerability of hAEC transplantation will be examined in 12 patients with compensated cirrhosis (**Figure 1**). They will be divided into four cohorts. Each cohort will include three patients treated sequentially (patient 1, then patient 2, then patient 3). Each patient will be observed for serious adverse events (SAEs) for 5 days post intravenous (IV) hAEC infusion before the next patient is enrolled. In Cohort 1, three patients will receive hAEC (0.5 × 10^6^/kg) as a single IV injection. If no SAE occur within 5 days of the last infusion in Cohort 1, a further three patients will be sequentially enrolled in Cohort 2 and receive a higher hAEC dose (1.0 × 10^6^/kg) as a single IV injection. If no SAE occur within 5 days of the last infusion in Cohort 2, a further three patients will be sequentially enrolled in Cohort 3 and receive the same hAEC dose as Cohort 2 (1.0 × 10^6^/kg) as a single IV injection at days 0 and 28. If no SAE occur within 5 days of the last infusion in Cohort 3, a further three patients will be sequentially enrolled in Cohort 4 and receive the same hAEC dose as Cohort 3 (1.0 × 10^6^/kg) as a single IV injection at days 0, 28, and 56 (**Table 1**).

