### Serious Adverse Event Reporting

All SAEs that occur after hAEC administration (whether or not considered related to hAEC) will be reported within 24 h to the DSMB. Promptly after the occurrence of the event, the treating physician would submit an initial written report of any SAE to the HREC. Any necessary follow-up will be submitted within a reasonable time thereafter.

The independent DSMB will review each SAE report and evaluate the relationship of the SAE to hAEC and determine a need for further action. If the discovery of a new adverse event related to hAEC raises concern over the safety of continued administration of the drug, the DSMB and PI will take immediate steps to notify the regulatory authorities, HREC and all physicians who have treated patients with hAECs.

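### The mandatory dechallenge criterion for Probable leaves some well-supported hAEC-related events, fatal, persistent or not assessable for dechallenge, without a causality category

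*Protocol article*

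**What the plan says.** The section Adverse Event Severity and Relationship to hAEC gives four levels: Unrelated, Unlikely, Possible and Probable. Each of the last three has a numbered list and states how many of its items are compulsory.

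- **Probable**: "An adverse event may be considered probable, if (must have the first three". The three are a reasonable time sequence, then "It cannot be reasonably explained by the known characteristics of the patient’s clinical state, environment or toxic factors, or other modes of therapy", then "It disappears or decreases on cessation or reduction in dose".
- **Possible**: "An adverse event may be considered possibly related if or when (must have the first two". The two are a reasonable time sequence and "It may have been produced by the patient’s clinical state, environment or toxic factors, or other modes of therapy administered to the patient". The introductory sentence describes the link as one that seems improbable but cannot be excluded.
- **Unlikely**: two compulsory items, an unreasonable time sequence and a ready alternative cause.
- **Unrelated**: a clear and indisputable outside cause.

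There is no not-applicable option for dechallenge.

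Under Study Design, in Cohort 1 "three patients will receive hAEC (0.5 × 10^6^/kg) as a single IV injection". Cohort 2 also receives one infusion per patient, Cohort 3 two and Cohort 4 three.

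Two other sections use attribution. Data Collection and Analyses pauses recruitment if "significant adverse events are noted directly or indirectly attributable to the hAECs". Serious Adverse Event Reporting starts its notification sentence with "If the discovery of a new adverse event related to hAEC raises concern over the safety of continued administration of the drug".

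**The concern.** The third criterion for Probable suits a drug that can be withdrawn or reduced while the patient is watched. Here the product is a cell infusion. Once it is complete, the cells cannot be withdrawn, and half the patients have no later dose to withhold. A death cannot improve on cessation, and neither can lasting harm, yet the same section grades death as Grade 5 and the SAE definition includes persistent disability.

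Criterion 2 of Possible is in substance the reverse of criterion 2 of Probable. Failing Probable on dechallenge therefore does not move an event down to Possible, because the absence of another explanation also rules Possible out.

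At stake is the attribution of events in a 12-patient study whose primary objective is safety and tolerability and whose data are meant to inform phases 2 and 3. With so few patients, one event left unrated, or rated as a link that seems improbable, changes the reported profile.

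**Working it through.** The article gives no figure to reproduce. The check has two parts: apply the compulsory criteria to every type of event, and count the exposure.

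**1. Categories against events.** Let T = timing is reasonable, A = another explanation is reasonable, D = the event improves on cessation or dose reduction. An event for which D cannot be assessed does not satisfy a compulsory D. The compulsory criteria reduce to:

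- Unlikely: not T, and A
- Possible: T and A
- Probable: T, not A, and D
- Unrelated: an indisputable outside cause, which cannot hold when A is absent

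| T | A | D | Category as written | Category if D is not compulsory |
|---|---|---|---|---|
| yes | yes | either | Possible | Possible |
| yes | no | yes | Probable | Probable |
| yes | no | no or not assessable | **none** | Probable |
| no | yes | either | Unlikely | Unlikely |
| no | no | either | none | none |

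The third row is the point. The event fails Unlikely on timing and on alternative cause, Possible on alternative cause, Probable on dechallenge, and Unrelated because no outside cause is evident. Removing the compulsion from D moves it to Probable and changes no other row.

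The last row is a separate, smaller gap (unreasonable timing and no other explanation). The change to D does not close it.

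**2. Exposure, from Study Design.** There are four cohorts of 3 patients, with 1, 1, 2 and 3 infusions per patient.

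- Planned infusions: 3×1 + 3×1 + 3×2 + 3×3 = 3 + 3 + 6 + 9 = 21
- Patients with a single infusion: 3 + 3 = 6 of 12
- Infusions that are a patient's only or last: one per patient = 12, and 12/21 = 57%
- Infusions followed by a further planned dose: 21 − 12 = 9

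After 12 of the 21 infusions there is no later dose to stop or reduce. After the other 9 a later dose could be withheld, although the cells already given remain.

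**The case against.** The case on the other side has four parts, and much of it stands.

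*Dechallenge is not always impossible.* A reader might infer that no event after a single infusion can reach Probable. The text does not support that. A reaction that subsides when an infusion is interrupted meets criterion 3, and one that resolves once the infusion has ended can reasonably be read as meeting it. Many listed primary outcomes (skin reactions, anaphylaxis, blood pressure or rhythm changes) are of this acute kind. The gap is confined to events that are fatal, persist, or begin after a completed infusion and cannot be assessed for dechallenge.

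*The safeguards do not rest on the label.* A reader might infer that recruitment stops and notification require a Probable rating. Neither section refers to the causality categories. The recruitment stop uses a broad test that includes indirect attribution. Every SAE goes to the DSMB within 24 h whether or not it is considered related, and the DSMB judges the relationship itself. Escalation counts any SAE within 5 days of the cohort's last infusion, without a causality condition. Fatal and disabling events are SAEs, so they reach independent review under any label.

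*The direction is not towards unrelated.* A reader might infer a bias towards that label. The event fails Unrelated and Unlikely, so the likely fallback is Possible. That understates the link but does not deny it.

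*A scale without a Definite level is not an error.* Agreed. Four levels are a legitimate choice.

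These arguments limit the consequence but do not remove the gap. The escalation rule covers 5 days and only SAEs, and the automatic referral to the DSMB covers only SAEs. Several primary outcomes (raised liver enzymes, raised INR, reduced eGFR) may be non-serious. For non-serious events, and to a lesser degree for events after day 5, the investigator's causality rating is a natural input to the attribution-based stop. Nor can the gap be put down to the brevity of an article, because the scale is printed with its compulsory counts.

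**Conclusion.** The point holds as a defect in stated wording. An event with reasonable timing, no other reasonable explanation and no assessable or observed improvement on cessation or dose reduction has no category. If the assessor forces one, it is Possible, whose description contradicts the finding that nothing else explains the event.

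The effect is on the causality tables for the primary safety objective. The rating may also inform the attribution-based recruitment stop, mainly for non-serious events and events after day 5. It does not affect SAE-based escalation or the DSMB's review of SAEs.

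The size cannot be given as a number of misclassified events, because the article gives no expected event rates. The 6 of 12 patients and 12 of 21 infusions show where no later dose exists; they are not the share of events affected.

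The conclusion assumes that assessors apply the compulsory lists literally and that no fuller document adds a not-applicable rule.

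**What to change.** In Adverse Event Severity and Relationship to hAEC, make criterion 3 of Probable supportive, or compulsory only where dechallenge can be assessed. State that it is not applicable after a completed or last infusion where dechallenge cannot be assessed, and for a fatal or irreversible event. An event meeting criteria 1 and 2 could then be rated Probable.

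Check that the attribution wording in Data Collection and Analyses and in Serious Adverse Event Reporting is consistent with the revised categories. The stopping rule itself need not and should not change for this purpose.

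The cost is a one-paragraph amendment and a matching label on the case report form, with no change to dosing, sample size or visits. The downside is that a few more events may be rated Probable.
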